# ‘MATRI-SUMAN’ a capacity building and text messaging intervention to enhance maternal and child health service utilization among pregnant women from rural Nepal: study protocol for a cluster randomised controlled trial

**DOI:** 10.1186/s12913-018-3223-6

**Published:** 2018-06-14

**Keywords:** FCHV, Capacity building, Text messaging, MCH service utilization, Nepal

## Abstract

**Background:**

Capacity development of health volunteers and text messaging to pregnant women through mobile phones have shown improved maternal and child health (MCH) outcomes and is associated with increased utilisation of MCH services. However, such interventions are uncommon in Nepal. We aim to carry out an intervention with the hypothesis that capacity building and text messaging intervention will increase the MCH service utilisation.

**Method/design:**

MATRI-SUMAN is a 12-month cluster randomized controlled trial (RCT). The trial involves pregnant women from 52 clusters of six village development committees (VDCs) covering 66,000 populations of Dhanusha district of Nepal. In the intervention clusters, Female Community Health Volunteers (FCHVs) will receive capacity development skills through reinforcement training, supervision and monitoring skills for the promotion of health seeking behaviour among pregnant women and study participants will receive periodic promotional text messaging service about MCH components through mobile phones. A sample of 354with equal numbers in each study arm is estimated using power calculation formula. The primary outcomes of this study are the rate of utilization of skilled birth attendants and consumption of a specified diversified meal. The secondary outcomes are: four antenatal (ANC) visits, weight gain of women during pregnancy, delivery of a baby at the health facility, postnatal care (PNC) visits, positive changes in child feeding practices among mothers, performance of FCHVs in MCH service utilization.

**Discussion:**

The intervention is designed to enhance the capacity of health volunteers for the promotion of health seeking behaviour among pregnant women and text messaging through a mobile phone to expecting mothers to increase MCH service utilization. The trial if proven effective will have policy implications in poor resource settings.

**Trial registration:**

ISRCTN60684155, (10.1186/ISRCTN60684155). The trial was registered retrospectively.

**Electronic supplementary material:**

The online version of this article (10.1186/s12913-018-3223-6) contains supplementary material, which is available to authorized users.

## Background

Maternal mortality is still the second largest causes of death among women:1 in every 180 women have chances of dying from maternal causes despite remarkable progress over the past decade [1]. Global communities have moved onto a new agenda of Sustainable Development Goals (SDGs) to ensure healthy lives and promote well-being for all at all ages and SDGs goal 3 targets to reduce the global maternal mortality ratio to less than 70 per 100,000 live births by 2030 [2, 3]. Despite a significant reduction of maternal death, Nepal needs greater effort to achieve the recommended reduction of maternal mortality ratio set by SDGs as the current maternal mortality ratio in Nepal is 170 per 100,000 live births [4].

Nepal Demographic and Health Survey 2011 revealed that only half of pregnant women in Nepal managed to attend four Antenatal Care (ANC) visits as recommended, about two-thirds of births (63%) took place at home, and only 45% of the mothers had postnatal visits [4]. Studies from Nepal and Sri Lanka showed that the anthropometric assessment of mothers and intake of micronutrients during pregnancy are associated with reduced maternal and childhood morbidity and mortality [5, 6]. The role of Female Community Health Volunteers (FCHVs) to promote safe motherhood, child health, family planning, and other community-based health services have been widely recognised in Nepal [7, 8]. These types of health volunteers can contribute to the useful bridge between the community and the primary health care facilities [9].

Studies from several developing countries have demonstrated that the use of trained health volunteers can have potential health benefits to mothers and children, such as increased uptake of routine immunization, breastfeeding, reduction in maternal and child morbidity and mortality, and increases in family planning services [10]. A study from Nepal found that the utilization of trained community health volunteers contributed to an improved skills to identify and manage a range of common diseases such as diarrhoea, night blindness, malnutrition and acute respiratory infections [11]. In a neighbouring country (India), trained community mobilizers were able to identify and counsel at risk families and there was significant improvement of breastfeeding techniques and duration, and the reduction of severe malnutrition cases among young children [11, 12]. Similarly, studies from African countries also concurred above findings [13, 14]. These evidences suggest that capacity building of health volunteers (especially FCHVs) along with some educational interventions for mothers might have significant benefits to the society in improving MCH services.

In recent years, mobile phones for information and communication in health sector has been increasingly used and became more popular in the developed as well as developing nations [15]. A global survey by WHO identified that “mHealth” initiatives are used in several countries in different forms and level of applications [16]. Evidence showed that mobile text messaging to educate people about healthy living practices can have a good impact on disease prevention and control, development of positive health behaviour, and better health service utilization [17–19]. For example, two Tanzanian studies [20, 21] demonstrated that the rate of ANC visits and utilisation of skilled health workers during delivery was improved with the implementation of text messaging services in resource-poor settings. Therefore, we aim to evaluate the impact of text messaging services coupled with capacity building to FCHVs in improving MCH services in rural areas of resource constraint district of Nepal.

The objective of this study is to evaluate the effectiveness of capacity building training and technological interventions (text messaging) for MCH service utilisation among rural women during antenatal and postnatal periods. Specific research questions consist of FCHVs’ performance on MCH service, service utilisation by pregnant women, balanced diet intake by pregnant women and breastfeeding practices. We hypothesize that capacity building of health volunteers and text messaging to pregnant women about MCH services help to improve the performance of FCHVs for the provision of MCH services, and service utilisation (e.g., antenatal and postnatal visits) and intake of healthy balanced diet by women during their antenatal and postnatal periods.

## Methods

### Study setting

The study is conducted across 6 VDCs (52 wards) of Dhanusha district of Nepal. Dhanusha is one of the 75 districts of Nepal, which is situated in the southern part (also known as ‘Terai’ in local language). VDCs are the basic political unit of the district, which is further divided into nine smaller units called wards. Each ward functions as one cluster in our study. The study area is predominantly inhabited by rural communities with agriculture as a main source of occupation (particularly vegetable farming) and the study population are relatively stable.

The district borders with Siraha, Mahottari and Sindhuli districts in the east, west and north, respectively and India in the south. The main residents of the district are from the Maithili heritage and the adult literacy rate is 69%. Administratively, the district comprises one municipality and 101 VDCs with an estimated population of 754,777 in 2011 [22]. Each VDC consists of one government health facility. According to the skilled birth attendant (SBA) policy of Nepal, the health post serves as the first contact point (birthing centre) for institutional delivery [4, 23], with the deployment of at least one staff nurse. Azonal hospital (200 beds) and a private medical college act as referral hospitals for Dhanusha and adjoining districts [24, 25].

### Study population

The study population consists of pregnant women aged between 15 and 49 years in their second trimester (gestation period between 13 and28 weeks). Pregnancy status was confirmed by a validated pregnancy test report. The gestational age will be determined based on first date of last menstrual period by asking with the participant. The expected date of delivery (EDD) based on gestational age will be confirmed through physical examination of pregnant women by nursing staff. Women were excluded if they had the following characteristics: (a) those not planning to stay at the study site during pregnancy and postpartum, (b) any physical and mental disability (which can adversely influence the study results), (c) women who have miscarriage or still birth during recruitment process, and (d) woman who are not willing (to give consent) to participate in the study.

### Study design

This is a two-parallel arms **cluster RCT** in rural community settings, provided participants are eligible for the study. Participants are recruited from 52 study areas by research assistants with the help of FCHVs. Then participants are then randomly assigned into intervention group and control arms based on clusters with approximately equal number of participations in each group.

Baseline information is collected after allocation of the clusters in two groups. At the same time, one-day extensive reinforcement training to the FCHVs in the intervention arm is conducted. Intervention group will receive text messages in their mobile phones. The principal investigator is responsible for sending text messages to the participants once they are recruited in the study and this process will continue until the fifth-month after childbirth. There will be three assessments during follow-up period and the data will be collected during these assessment periods: between 38 and 39 weeks of gestation, during delivery, and at 7 months after child birth. During the follow-up period, monitoring and supervision of FCHVs in the intervention arm will also be done to assess their performance. Additionally, assessment of child will be carried out at birth and 7 months after birth [Fig. 1].

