### Sampling technique

We employed multi-stage cluster sampling. First, two health facilities (consisting of one primary health care centre and one health post) catchment area of Dhanusha district has been selected purposefully. We selected these health facilities because there have been no MCH-related services from other organizations before, but the governmental. Furthermore, no research work has been conducted yet relating to this field.

Second, six VDCs have been selected in the catchment area of these two health care facilities by stratified random sampling technique. The population of each VDC in the catchment area range from 3500 to 19,000. Therefore, VDCs in both health care facilities catchment areas have been stratified into three strata based on population size (< 5000, 5000–10,000, and > 10,000), forming a total of six strata. One VDC has been randomly selected from each stratum [24, 25]. Third, those selected six VDCs comprised of 54 wards (here we called cluster for our study) where two of them are excluded as these wards are situated in the town area. The reminder 52 clusters have been selected for a trial. Finally, the complete enumeration of all households with pregnant women in their 2nd trimester from these clusters has been carried out.

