### Identification and recruitment of participants

All households with pregnant women in 52 clusters have been identified and screened applying inclusion and exclusion criteria. The identification of pregnant women has been made with the help of FCHVs’ antenatal registers. Pregnant women from each household in have been registered by FCHVs in their respective ward. All pregnant women with gestational period between 13 to 28 weeks are included in the study. Each household is coded and marked in the outside wall with a visible unique serial number to track participants during follow-up period.

The baseline information of these pregnant women was collected between July and September 2015. Selection of participants has been done by trained female research assistants (FRA), who are fluent in both Nepali and Maithili languages. Written informed consent have been taken from each participant who are willing to participate in the study. Participants are informed about the purpose of the study, advantages and any potential harms arising from a study. Head of the family, usually husband or close relatives of the relevant participants, were also informed about the study. For any adverse event or inquiry by the participants will be entertained or clarified.

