### Data collection plan

The structured questionnaire has been piloted using responses from 20 households in the adjacent district. Necessary feedback is received and the amendment has been made in the final questionnaire before baseline data collection. Data will be collected by research assistants who are trained in the tools and techniques of data collection. Anthropometric assessment will be taken by six Female Research Assistants (FRAs) (one FRA per VDC).All measurements will be made three times and the median value will be recorded for analysis. The collection of information on pregnancy, outcomes and its determinants will be made longitudinally at different stages. The methods will employ structured interviews, FGD and anthropometric assessment.

Data will be collected at four chronological points. Baseline information on demographic characteristics, obstetric history, anthropometry, biochemical test, dietary survey and current practices on services utilization will be taken on 4–6 month prior to intervention. The reminders will be the follow-up period as described below;Assessment of pregnant women (services utilization, dietary survey, anthropometry and biochemical test) in the 9th month during intervention (Follow up- I).Data on birth weight will be taken by FRAs preferably within the first hour of the birth (Follow up II).Assessment of mother and child (services utilization, dietary survey and anthropometry including maternal and child morbidity) and satisfaction of the participants at the7th month after intervention (Follow up III).

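### Baseline is collected after ward allocation, alongside training of intervention-arm FCHVs and without stated blinding, and the article gives no single order for consent, allocation, baseline and first message

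*Protocol article*

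**What the plan says.** All references are to the Methods of the protocol article.

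- **Study design.** On recruitment: "Participants are recruited from 52 study areas by research assistants with the help of FCHVs". On the next step: "Then participants are then randomly assigned into intervention group and control arms based on clusters". On baseline and training: "Baseline information is collected after allocation of the clusters in two groups. At the same time, one-day extensive reinforcement training to the FCHVs" of the intervention arm is conducted.
- **Identification and recruitment of participants.** "The identification of pregnant women has been made with the help of FCHVs’ antenatal registers". Trained female research assistants make the selection and written consent is taken. Baseline is dated July to September 2015; consent is not dated.
- **Sampling technique.** "the complete enumeration of all households with pregnant women in their 2nd trimester from these clusters has been carried out".
- **Randomization.** Researchers and participants are not blinded. Data collectors are to be blinded at follow-up; nothing is said about baseline.
- **Text messaging through a mobile phone.** Messages start woman by woman, as soon as she has been recruited and allocated.
- **Data collection plan.** Baseline, including the dietary survey and "current practices on services utilization will be taken on 4–6 month prior to intervention".

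**The concern.** In a cluster trial, allocation of the wards protects the comparison only if nobody who can influence enrolment or baseline answers knows the arm, or if enrolment and baseline are finished before the arm is known. Here baseline follows allocation by the article's own statement, and it coincides with an event, the training, that tells intervention-arm volunteers which arm they are in.

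Two things are at stake, and they are not equally well founded.

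1. **Baseline reporting.** Dietary diversity and service use at baseline are self-reported. Diet is a co-primary outcome, and repeated dietary measures are to be analysed with GEE and mixed models. An arm-related reporting difference at baseline would carry into any estimate that uses that baseline.
2. **Recruitment.** If consent was still being taken after the arm was known, women could be listed, judged eligible or persuaded differently by arm. Intention-to-treat does not repair this, because it starts from the women who were enrolled.

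**Working it through.** **Step 1. Set the statements on order side by side.**

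| Section | Order stated or implied |
|---|---|
| Study design | recruitment, then assignment by cluster, then baseline with training at the same time |
| Matching | pairs formed before baseline from facility and volunteer records, in consultation with the ward's FCHV |
| Identification and recruitment | selection and consent described beside the July–September 2015 baseline; only baseline is dated |
| Text messaging | recruitment and allocation, then messages at once, per woman |
| Data collection plan | baseline before the intervention |

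**Step 2. Baseline against knowledge of arm.** Study design puts baseline after allocation. Randomization states no blinding of researchers or participants, and limits data-collector blinding to follow-up. So no stated safeguard keeps the arm from those asking or answering the baseline questions. This needs no inference about recruitment.

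**Step 3. Baseline against the intervention.** If baseline follows allocation and messages start at once after recruitment and allocation, neither Study design nor Text messaging puts baseline before a woman's first message. Only the Data collection plan does. Its reference to months 4–6 probably means months of pregnancy, since the next assessment is in the 9th month.

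**Step 4. Which analyses are exposed.** Skilled birth attendance at the index delivery has no baseline value to distort. The confounder adjustment named in the Data management and analysis plan concerns weight gain and haemoglobin and includes socio-demographic characteristics, which training cannot alter. The exposed item is mainly repeated diet. If reported baseline diet differs between arms by *e* through knowledge of arm alone, a change-from-baseline comparison shifts by −*e*, and a covariate-adjusted one by −*βe*, where *β* is the slope on baseline. The documents give neither *e* nor its sign.

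**Step 5. Recruitment against allocation.** Study design puts recruitment first. Pointing the other way:
- Matching used records, so wards could be randomised before any woman consented.
- Messages start on an individual basis, which fits staggered enrolment.
- One exclusion, in Study population, refers to pregnancy loss during the recruitment process, so recruitment took time.

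None of these states that consent followed allocation. They only allow it.

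**Step 6. An illustration of size, if consent did follow disclosure.**

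The plan's own sample size first (Sample size estimation: 12% versus 32%, power 0.80, two-sided 0.05, design effect 2.29):

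- n = (1.960 + 0.842)² × [0.12 × 0.88 + 0.32 × 0.68] / 0.20² = 63.4, rounded up to 64
- 64 × 2.29 = 146.6, rounded up to 147 per arm, as stated
- Effective number per arm: 147 / 2.29 = 64.2

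Assume no true effect, a control rate of 12%, and an intervention-arm rate raised by *b* through selection alone. The chance of a significant result favouring the intervention is 1 − Φ[(1.96 × SE₀ − b) / SE₁], with SE₀ pooled and SE₁ unpooled. For b = 0.05, SE₀ = √(2 × 0.145 × 0.855 / 64.2) = 0.0621 and SE₁ = √((0.1056 + 0.1411) / 64.2) = 0.0620, so the argument is (0.1218 − 0.05) / 0.0620 = 1.16 and the chance is 12.3%.

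| Assumed b (points) | False result favouring intervention |
|---|---|
| 0 | 2.5% |
| 2 | 5.2% |
| 5 | 12.3% |
| 10 | 32.4% |

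For a sense of what yields such a *b*: if 5% to 15% of intervention women were preferentially enrolled with a 50% instead of a 12% chance of skilled attendance, b = 0.05 × 0.38 = 1.9 points to 0.15 × 0.38 = 5.7 points. Neither input comes from the documents.

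**The case against.** The strongest reply is that the sentence before the baseline statement puts recruitment ahead of assignment, and the text-messaging section names the two in the same order. Read literally, only data collection follows allocation, so the arm could not affect who was enrolled. Households were completely enumerated, all women in the gestational window were to be included, and research assistants, not volunteers, made the selection. The Data collection plan puts baseline before the intervention, and one day of volunteer training is unlikely to change a woman's diet by the time she is interviewed. The trial-design figure and the additional file on allocation, neither shown, may settle the order. Fieldwork is over, so reordering it is moot for this trial.

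Much of this stands. A reader might infer that women were recruited after disclosure and randomisation was undone, or that baseline values were already changed by the intervention. The documents support neither: the first is contradicted in Study design and the second in the Data collection plan.

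What the reply does not remove is the statement that baseline was collected after allocation, with no blinding stated for that stage. Enumeration and research-assistant selection reduce discretion without ending it: identification draws on the volunteers' registers, and consent, intention to stay and disability remain matters of judgement or persuasion. The conflict between sections also remains.

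**Conclusion.** The point holds in a limited form. It is stated, not inferred, that baseline was collected after ward allocation and alongside training of intervention-arm FCHVs, without stated blinding at that stage. Self-reported baseline diet and service use are therefore open to influence from knowledge of arm, more plausibly through reporting than through any immediate effect of training. The direction and size are unknown.

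Recruitment bias is a conditional risk. It requires that consent continued after allocation, which the sections on recruitment and text messaging permit and Study design contradicts, and it is limited by complete enumeration. The figures in the working are illustrative only: they assume both that condition and an imbalance that the documents do not supply, so they are not an estimate for this trial.

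This should be corrected, but it does not by itself invalidate the design. Confidence is moderate, because unseen supplementary material may clarify the order.

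**What to change.** **Order of steps.** State and follow one sequence: enumeration, eligibility, consent and baseline completed in both wards of a pair (354 / 26, about 14 women), then that pair's allocation disclosed, then FCHV training and messages. Reconcile Study design, Identification and recruitment, Text messaging and the Data collection plan to it. This needs no extra staff; the small downside is a slightly later start of training and messages in some wards.

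**Fieldwork already done, as in this trial.**
- Report women listed, eligible and consenting by arm, with dates of consent, baseline, disclosure of allocation and first message. The cost is tabulation from existing records, if those dates were kept.
- Keep intention-to-treat on all enrolled women in their allocated ward. The enumeration list serves flow reporting; as an analysis set it would bring in ineligible and non-consenting women for whom no outcomes were planned.
- Add a sensitivity analysis, applied identically in both arms, that does not adjust for self-reported baseline diet and service use collected after allocation. It may lose some precision. Do not discard only the baseline values taken after training: only one arm was trained, so this would create missing baselines in that arm alone.

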### Potential contamination

Most of the clusters are geographically separated and that the distance between clusters are at least 500 m from each other which may prevent the possible treatment contamination between intervention and control arms. There may be potential contamination due to sharing of training knowledge but knowledge is not equal to implementation, moreover, the control group FCHVs will not be followed-up by our FRAs. The likely contamination of text messaging through mobile phone to the pregnant women will be confirmed by asking whether they received MCH information from the intervention area during follow-up period.

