##### Supervision and monitoring

A monthly visit to FCHVs in the intervention areas will be made by researchers using supervision and monitoring format adopted from “Bal Parivar Mitra” monitoring format for the CB-MCHN project (motivation for change) in India [28]. The FCHVs will be assessed by researchers against their performance on MCH services delivery (Additional file 2).

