Both the intervention and control groups will receive regular antenatal and postnatal care provided by the government through local health facilities. These services are free of cost at the point of delivery. Both intervention and control arms participants should make at least four ANC visits (first within 4 months, second within 6 months, third within 8 months and fourth within 9 months, respectively in nearby health facility) and three home visits (First visit at day one, second at day 3 and third at day 7) in the first 7 days after childbirth by FCHVs/CHWs as part of postnatal care service.

**Usual care:** FCHVs in the control clusters will not receive training on the MCH service package and participants (pregnant women) also will not receive any text message during study period. There will be no supervision to the FCHVs from the project side, but the monthly visit by MCHWs/CHWs to them has been made from the government side as part of regular supervision to collect integrated community health service reports including MCH service reports. Any adverse event.

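### The only FCHV performance assessment described is a supervision format used in the intervention arm, so it cannot support a between-arm comparison of this secondary outcome

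*Protocol article*

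**What the plan says.** The abstract lists "performance of FCHVs in MCH service utilization" among the secondary outcomes, and the Outcome measures section lists FCHV performance again, leaving the details to Additional file 5. The last paragraph of the Background hypothesises that the intervention will "help to improve the performance of FCHVs for the provision of MCH services". The Data management and analysis plan assigns logistic regression to the primary and secondary outcomes and makes no exception for this one.

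On measurement, the Study design section says that "monitoring and supervision of FCHVs in the intervention arm will also be done to assess their performance". The Supervision and monitoring section adds: "A monthly visit to FCHVs in the intervention areas will be made by researchers using supervision and monitoring format". It continues: "The FCHVs will be assessed by researchers against their performance on MCH services delivery", with the form in Additional file 2.

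On the control arm, Potential contamination says that "the control group FCHVs will not be followed-up by our FRAs". The usual-care paragraph, at the end of the section on text messaging, says: "There will be no supervision to the FCHVs from the project side". It then describes a monthly government visit that collects routine service reports from control FCHVs.

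**The concern.** An outcome that is to show an effect of a randomised intervention has to be measured in the same way in both arms. Here the described assessment is assigned to the intervention arm, and project contact with control FCHVs is deliberately withheld.

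There is a second problem. The assessment is made at the supervision visit, and supervision is one of the two parts of FCHV capacity building. Treatment and measurement are therefore the same act, carried out by people who know the allocation.

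At stake is how the result would be read. A rise in scores over the monthly visits could be reported as a randomised secondary finding in support of a stated hypothesis, although randomisation gives it no protection.

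**Working it through.** No calculation bears on this point. The check is to follow the outcome from hypothesis to measurement to analysis and see which arm supplies data.

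1. **Status of the outcome.** FCHV performance is in the hypothesis (Background), in both outcome lists (Abstract and Outcome measures), and within the scope of the planned regression (Data management and analysis plan). It is treated as an effect to be estimated, not as a process record.

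2. **Where the described assessment takes place.** Study design places it in the intervention arm, and Supervision and monitoring places it in the intervention areas. From Matching, 52 clusters form 26 pairs, giving 26 wards per arm. The format is therefore used in 26 of 26 intervention wards and 0 of 26 control wards.

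3. **Whether another described instrument fills the gap.**
   - Questionnaires (Research instruments) and the four data collection points (Data collection plan) concern women and their children. The article does not say whether women are asked about contacts with their FCHV.
   - Focus groups explore views and beliefs, not performance.
   - The pre- and post-test (Reinforcement training) measures the knowledge of trainees, who are intervention FCHVs only.
   - FCHV antenatal registers were used for recruitment in all 52 clusters (Identification and recruitment of participants), and FCHV and facility records were obtained before the trial (Matching). Government monthly reports come from control FCHVs (usual care). The article names none of these as the source for this outcome.

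4. **Who assesses.** Supervision and monitoring says researchers; Potential contamination implies that female research assistants follow up the intervention FCHVs. Randomization states that researchers are not blinded. The blinding promised there for follow-up data collectors cannot extend to this assessment, since a project supervision visit happens in one arm only and so reveals the allocation.

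5. **What the data can estimate.** With scores from one arm, the available quantity is the change over time in that arm. It combines any effect of training and supervision with calendar trend, familiarity with a repeated form and assessor expectation. With no control scores, these parts cannot be separated. A between-arm difference cannot be computed from this format.

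**The case against.** The strongest reply is that the article never says that the supervision format is the secondary outcome. The definition is in Additional file 5 and the form in Additional file 2, neither of which was available, and an article may leave such detail to its supplements. The abstract's wording could describe a service measure taken from registers or from women in both arms. The statements about control FCHVs withhold supervision and follow-up; they do not say that no data on their work will be obtained.

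Much of this stands. A reader might infer that no between-arm comparison of FCHV performance is possible at all. The documents do not support that: registers and government monthly reports exist in control wards, and a both-arm definition may be in Additional file 5. Nor does the whole hypothesis fail, since its clauses on service use and diet are measured in women in both arms.

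What does not stand is that this is mere condensation. The article positively states where performance is assessed, and that is one arm. A both-arm source in Additional file 5 need not conflict with withholding supervision from controls, but it would have to be reconciled with the Study design sentence that ties performance assessment to the intervention arm.

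It can also be said that the trial is reported as completed, so control FCHVs can no longer be assessed prospectively. That narrows the remedies but does not remove them.

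**Conclusion.** The point holds for the assessment that the article describes. It covers 26 intervention wards and no control wards, is made by unblinded researchers and is part of the treatment. It cannot support a between-arm comparison, and any change it shows is an uncontrolled time trend under repeated supervision.

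The damage is limited to one secondary outcome and one clause of the hypothesis. Both primary outcomes are untouched. The conclusion assumes that the supervision format is the intended source of the outcome, which the article suggests but does not state; Additional file 5 would settle it. The change should be made before any result on FCHV performance is presented as an effect of the intervention.

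**What to change.** - Reconcile Study design, Potential contamination, Supervision and monitoring and the usual-care paragraph with the outcome definition in Additional file 5, and state the source for each arm.
- Base the between-arm outcome on a source with the same form in both arms: FCHV registers or the government monthly service reports. Analyse it at ward level, respecting the 26 matched pairs.
- Use women's reports of FCHV contacts only if the questionnaires actually collected them.
- Label the supervision format as intervention-arm process data.
- If no both-arm source is used, withdraw the comparative claim about FCHV performance.
- Since the trial is completed, disclose any definition that was not already in Additional file 5 as one made later.

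The cost is abstraction of existing routine records in both arms; relabelling alone needs no new data. Two limits should be disclosed: routine records are coarser than the project's form, and training may change how FCHVs record as well as what they do, so a difference in records need not be a difference in practice.
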